## Abstract

**Background:**

The Danish OPUS I trial randomized 547 patients with first-episode psychosis to a two-year early-specialised assertive treatment programme (OPUS) versus standard treatment. The two years OPUS treatment had significant positive effects on psychotic and negative symptoms, secondary substance abuse, treatment adherence, lower dosage of antipsychotic medication, and a higher treatment satisfaction. However, three years after end of the OPUS treatment, the positive clinical effects were not sustained, except that OPUS-treated patients were significantly less likely to be institutionalised compared with standard-treated patients. The major objective of the OPUS II trial is to evaluate the effects of five years of OPUS treatment versus two years of OPUS treatment.

**Methods:**

The OPUS II trial is designed as a randomized, open label, parallel group trial with blinded outcome assessment. Based on our sample size estimation, 400 patients treated in OPUS for two years will be randomized to further three years of OPUS treatment versus standard treatment. The specialized assertive OPUS treatment consists of three core elements: assertive community treatment, psycho-educational family treatment, and social skills training.

**Discussion:**

It has been hypothesized that there is a critical period from onset up to five years, which represents a window of opportunity where a long-term course can be influenced. Extending the specialized assertive OPUS treatment up to five years may allow the beneficial effects to continue beyond the high-risk period, through consolidation of improved social and functional outcome.

**Trial registration:**

Clinical Trial.gov NCT00914238

## Background

The yearly incidence of patients aged 18 to 35 years with schizophrenia in Denmark in 2008 was approximately 800. The yearly incidence for patients of the same age with other disorders in the schizophrenia spectrum (F 21 - F 29, ICD -10[1]) was almost 500. Schizophrenia is a severe neurodevelopmental disorder with complex neuronal and psychosocial pathogenesis. The first psychotic break down is usually seen in adolescence or early adulthood and has a serious impact on young peoples' lives through interference with their social lives and work. Furthermore, patients with psychosis often suffer from substance abuse, depression [2], suicide [3], and are often associated with high rates of violence and legal problems[4]. The direct cost of schizophrenia in European countries has been estimated to two percent of the national health expenditures[5], - a similar order of magnitude to cancer or ischaemic heart disease. Moreover, there are also huge indirect costs to society in terms of suffering of relatives and lost productivity[5].

The focus on first-episode psychosis arises because converging evidence suggest that the underlying illness process that affects biological, psychological, and social domains undergo major deterioration around the onset phase of the illness[6-8]. Delayed detection and treatment is a widespread problem and predicts poor clinical outcome [9,8]. The association between longer periods of untreated psychosis and poorer outcomes is firmly established[8,9]. It is therefore of utmost importance to identify possibilities for prevention and treatment. The evidence base for the psychosocial treatment of psychotic disorders is still underdeveloped[10]. Historically, randomized clinical trials have been few in number and uneven in quality[11]. There is an urgent need for large investigator-initiated, independent, non-commercial trials of complex interventions that can help us prevent the invalidating and deteriorating course in many patients.

The Danish OPUS I trial randomized 547 patients with first-episode psychosis to a two-year specialised intensive assertive treatment programme (OPUS) consisting of a multimodal phase-specific treatment of first episode psychosis versus standard treatment[12]. The results significantly favoured the OPUS treatment[12], showing positive effects on psychotic and negative symptoms, secondary substance abuse, treatment adherence, lower dosage of antipsychotic medication, and a higher treatment satisfaction after two years of treatment. However, the five-years follow up study, three years after patients from OPUS were transferred to standard treatment, showed that most of the positive clinical effects were not sustained[13]. This concurs with the British LEO trial[14,12], demonstrating that specialised treatment for people with first-episode psychosis is effective on psychotic and negative symptoms only as long as the treatment continues.

It has been hypothesised that there is a critical period up to five years after onset of psychotic illness, which represents a window of opportunity where the long-term course can be influenced[6]. The objective of the present OPUS-II trial is therefore to carry out a comparison of five-years versus two-years of specialised assertive intervention for first episode psychosis. Our hypothesis is that extending the specialised assertive intervention service up to five years will allow the beneficial effects to continue beyond this high-risk period, through consolidation of improved social and functional outcomes. The trial will thereby provide clinicians and planners of mental health services with the needed evidence regarding the optimal duration of specialised treatment of first-episode psychosis patients. The cost-benefit of a specialised assertive intervention sustained for the entire critical period is equally important to establish.

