#### Exclusion criteria

patients whose diagnosis was evaluated retrospectively and found not to fulfil the criteria for first-episode psychosis in the F2-spectrum (ICD 10) at any time during the first 11/2 year of OPUS treatment, and patients who do not give signed informed consent to participate in the trial. Drug and alcohol misuse will not lead to exclusion. Patients who are mentally retarded in moderate to severe degree are not treated in OPUS teams and are therefore not a part of the inclusions and exclusions criteria.

Randomization will take place approximately six months prior to the termination of the original two-year OPUS treatment. This will allow a gentle transfer to other treatment services for the control group, and allow proper time to plan the future course of treatment for the experimental group. Expected duration of participating in the trial is therefore 3 1/2 year from entry interview to follow-up interview.

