### Outcome measures

The primary outcome measure is: negative symptoms measured with schedule for assessment of negative symptoms in schizophrenia (SANS[17]). Investigators at entry and at the 31/2 years follow-up interview will be independent and blinded for treatment allocation. Through training interviews, we will ensure that the assessors have a high level of interrater reliability with kappa values for primary outcome measure of at least 0.70, prior to beginning the trial. We will also ensure that assessors have an interclass correlation coefficient (ICC) of at least 0.70 regarding SANS global scores. ICC is calculated in SPSS using two-way mixed models for absolute agreement on single measures.

The secondary outcome measures are: simultaneously remission of both negative and psychotic symptoms, measured with SANS and schedule for assessment of positive symptoms in schizophrenia (SAPS[17]), psychotic symptoms measured as continuous measures, substance abuse, working alliance, self efficacy, user satisfaction, adherence to treatment, compliance with medication, suicidal behaviour, use of bed days, ability to live independently, and labour market affiliation. The criteria for remission are that none of the global measures of severity in SAPS (global scale for hallucinations, delusions, bizarre behaviour, or thought disorder) and SANS (global scale for anhedonia, avolition, alogia, and affective blunting) exceeds a value of 2 (2 = mild symptoms). All outcome measures are measured with validated scales (Table 1). These outcomes will be assessed at baseline and at follow-up. Through training interviews, we will also ensure that assessors have an ICC coefficient of at least 0.70 regarding SAPS global scores.

**Table 1 T1:** Assessment instruments in the OPUS-II trial.

Topic:	Instrument:
Psychopathology	Schedules for Clinical Assessment in Neuropsychiatry (SCAN)[28], Schedule for assessment of positive and negative symptoms in schizophrenia (SAPS and SANS[17])[29], Hamilton's depressions scale[30], Suicidal behaviour, DUP, Duration of Untreated Psychosis[31]

Social function	Personal and Social Performance scale, PSP[32] Global Assessment of Functioning, GAF[33]

Cognitive function	Brief Assessment of Cognition in Schizophrenia, BACS [34]

Medication and side effect	The UKU side effects rating scale, UKU[35] Patients self rapport

Selfefficacy	General Self - efficacy Scale[36]

Alliance	Working Alliance Inventory, client, WAI[37]

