### Sample size calculation

In the OPUS I trial we found that the patients treated in OPUS had a mean score of 1.42 in negative dimension and patients treated in standard treatment had a mean score of 1.84 in negative dimension with standard deviation of 1.2[22,12]. In this present OPUS II trial we want to be able to detect a difference of 0.4 point in negative dimension, measured with SANS. We are thus planning a trial of a continuous response variable from independent control and experimental participants with one control per experimental participant. If the true difference in the experimental and control means is 0.4 with a standard deviation of 1.2, we will need to study 142 experimental participants and 142 control participants to be able to reject the null hypothesis that the population means of the experimental and control groups are equal with probability (power) 0.80. The type I error probability associated with this test of this null hypothesis is 0.05, and 200 patients will be included in each intervention group because we expect approximately 30% attrition.

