### Data analyses

The primary outcome measure, negative symptoms, will, as other continuous outcome measures, be subjected to analysis using a mixed-model analysis with a repeated measurements model with unstructured variance matrix, using the mixed-model command in SPSS. This approach assumes that the distribution of missing data can be estimated from the information from previous interviews and from information about other patients in the database. The condition for using this method is the assumption that data are missing at random or missing completely at random when taking into consideration the information extracted from baseline interviews and information about the other patients in the database. In this model, baseline values of the scales are included. Variables included as covariates will be site (six different teams), sex, co-morbid substance abuse, baseline values of the remission variable, and the baseline values of variables that differ significantly in drop-out analyses. Besides the above-mentioned variables, compliance with medication, level of school education, and whether or not a family member is involved in treatment will be included in analyses of differences between patients that are lost to follow-up and those who remain in the trial. If significant, these variables will be included as covariates.

For evaluation of the dichotomous secondary outcome measure (simultaneously remission of psychotic and negative symptoms or not), we will use multiple multivariate imputations, using all other covariates to impute a distribution of missing values. The dichotomous outcomes will be analysed with logistic regression analyses. Variables included as covariates will be the same as those included in analyses of continuous measures. Similar to the repeated measurement, the condition for using multiple imputations is that data are missing at random or missing completely at random, when taking into consideration the information extracted from baseline interviews and information about the other patients in the database.

Analysis will be based on the intention-to-treat principle. Data from all patients will be included in the group to which random assignment is made, regardless of intervention received.

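### Duration of untreated psychosis is called an established predictor of outcome and is collected, but the covariate and imputation rules leave it out (minor)

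*Protocol article*

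**What the plan says.** In the Background the article writes: "The association between longer periods of untreated psychosis and poorer outcomes is firmly established". Table 1, under Outcome measures, lists "DUP, Duration of Untreated Psychosis" among the psychopathology assessments, so the variable will be in the database.

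The Data analyses section then commits to a covariate list for the continuous outcomes, including the primary one: "Variables included as covariates will be site (six different teams), sex, co-morbid substance abuse, baseline values of the remission variable". The baseline value of the scale is also in the model. Variables that differ significantly between completers and drop-outs are to be added. The candidates for that comparison are the variables already listed plus medication compliance, school education and family involvement in treatment. The logistic models take the same covariates, and the multiple imputation for the remission outcome draws on the covariates as well. DUP is on neither list.

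**The concern.** The article singles out one patient-history variable as an established predictor of outcome and collects it. It then adjusts for variables such as sex and schooling, for which it makes no comparable claim, and not for DUP. DUP is fixed before randomisation, so nothing prevents its use.

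Two things are at stake. First, a covariate that predicts follow-up SANS beyond those already in the model would narrow the confidence interval for the primary comparison. Second, the mixed model and the imputation both rely on data being missing at random given what they contain, and about 30% of patients are expected to be lost. A known predictor of outcome is a natural member of that conditioning set. Under the stated rule even the listed candidates get in only if a drop-out test is significant, and DUP is not a listed candidate.

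**Working it through.** **1. Is there any route for DUP into the models?** The fixed list does not name it. The rule on drop-out variables could be read as open-ended, but the article goes on to name the candidates, and DUP is not among them. The imputation is described as using the other covariates, which refers back to the same list. So for the models described, the answer is no. No model is described for register outcomes such as bed days, so nothing can be said about those.

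**2. The plan's own figure.** Inputs from Sample size calculation: "If the true difference in the experimental and control means is 0.4 with a standard deviation of 1.2"; "The type I error probability associated with this test of this null hypothesis is 0.05"; power 0.80; equal allocation. Taking the test as two-sided (the article does not say):

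n per arm = 2 × (1.960 + 0.842)² × 1.2² / 0.4² = 2 × 7.849 × 9 = 141.3, rounded up to 142.

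This matches the stated 142 exactly (one-sided would give 112). It uses the unadjusted SD of 1.2, so it does not rely on DUP or any other covariate.

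**3. What DUP could add.** With 200 per arm and 30% attrition, 200 × 0.70 = 140 per arm remain. Let ρ be the correlation between baseline and follow-up SANS, and R² the share of the remaining variance that DUP explains. Neither is in the document; both are assumptions. Then

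SD = 1.2 × √(1 − ρ²) × √(1 − R²), SE = SD × √(2/140), power = Φ(0.4/SE − 1.960).

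The factor for ρ matters because the planned model already contains baseline SANS. DUP can only act on the variance left after that.

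| ρ | SD without DUP | Power without DUP | R² = 1% | R² = 2% | R² = 5% | R² = 10% |
|---|---|---|---|---|---|---|
| 0 (unadjusted) | 1.200 | 79.6% | 80.0% | 80.4% | 81.6% | 83.6% |
| 0.3 | 1.145 | 83.2% | 83.6% | 84.0% | 85.1% | 86.9% |
| 0.5 | 1.039 | 89.6% | 89.9% | 90.2% | 91.1% | 92.4% |
| 0.6 | 0.960 | 93.7% | 93.9% | 94.1% | 94.7% | 95.7% |

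At ρ = 0.5 the gain is about 0.3 points at R² = 1%, 1.4 points at 5% and 2.8 points at 10%. In terms of the confidence interval, √0.99 = 0.995 and √0.95 = 0.975, so it narrows by 0.5% to 2.5% over the 1% to 5% range.

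**4. Why the lower part of the range is more plausible.** Baseline is taken late: "Randomization will take place approximately six months prior to the termination of the original two-year OPUS treatment". Baseline SANS and baseline remission are therefore measured after about a year and a half of treatment. They should already carry much of what DUP says about prognosis. This is reasoning, not a figure from the article.

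**5. Could the trial test whether the effect depends on DUP?** For a treatment-by-DUP interaction with a median split, 70 per arm in each half and SD 1.2:

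SE = 1.2 × √(2/70 + 2/70) = 0.287; power for an interaction of 0.4 = Φ(0.4/0.287 − 1.960) = about 29%.

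An interaction of about 0.80, twice the target effect, is needed for 80% power. With SD 1.039 (ρ = 0.5), power for 0.4 is about 36%.

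**The case against.** The strongest reply is that this is a preference and not an error. The model already adjusts for the baseline scale, site, sex, substance abuse and baseline remission. Leaving out one more prognostic variable does not bias a randomised comparison in a linear model. The sample size never counted on DUP, and calling a variable prognostic does not oblige a plan to adjust for it. All of that stands, and it is why the point is minor. What remains is that the article does not leave covariates to a later document. It commits to a named list and a named set of candidates, and that list omits the variable its own Background stresses.

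A reader might go further. The article holds that "there is a critical period up to five years after onset of psychotic illness", while the treatment years are counted from the start of OPUS. One might infer that the critical-period rationale goes untested, that patients with long DUP dilute the effect, or that the article's phrase about covering the whole critical period holds only when DUP is zero. The document does not support these readings:

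- The stated objective is five versus two years of OPUS, and the trial tests that. The critical period is its motivation.
- The Background hypothesises that benefit carries on past the high-risk period. It does not confine benefit to it, so any dilution model would be the reader's own.
- Extension to five years of OPUS reaches the end of a five-year window counted from onset, whatever the DUP. Only the time before entry to the service is missed, and no treatment duration could cover that.
- Adding DUP as a main effect would not test the critical-period idea in any case. Only an interaction would, and a supportive analysis of that kind may properly be left to an analysis plan that is not shown.

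**Conclusion.** The point holds as a minor one. The covariate and imputation rules, as written, omit a pre-randomisation variable that the article collects and calls an established predictor. There is no bias in the randomised linear comparison, and the 142 per arm is correct.

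The benefit of including DUP is a small precision gain of unknown size: about 0.3 to 1.4 power points if the baseline SANS correlation is 0.5 and DUP explains 1% to 5% of the residual variance. Over assumed correlations of 0.3 to 0.6 and the same 1% to 5%, the gain runs from about 0.2 to 1.8 points. The missing-at-random assumption would be somewhat more credible under about 30% attrition; the article gives nothing from which to quantify that. The conclusion covers the mixed, logistic and imputation models described, not the register outcomes.

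**What to change.** In Data analyses, add baseline DUP on a log scale to the fixed covariates of the mixed model and the logistic models. Name it as a predictor in the multiple imputation. State that it is included whatever the drop-out tests show.

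The cost is one degree of freedom in each model and a stated way of handling missing DUP values. No new data are needed, and the sample size does not change. An analysis of treatment by time since onset is optional. If one is done, label it exploratory, given about 29% power for an interaction of 0.4.

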## Methods

### Design

The study is designed as a randomized, open label, parallel-group trial with blinded outcome assessment (Figure 1). Given the nature of the question, patients and health care providers cannot be kept blind to treatment allocation. There are five OPUS-teams in the Capital Region and one OPUS-team in Central Denmark Region.

**Figure 1 F1:**
[figure not shown]
**CONSORT diagram depicting flow of study participants in the OPUS II trial**.

### Participants

All patients treated within the Danish mental health services for at least 11/2 year by the six OPUS teams will be approached for eligibility. Patients must fulfil the ICD 10 diagnostic criteria for schizophrenia or schizophrenia-like psychosis (F2)[1].

#### Inclusion criteria

patients aged 18-37 years with first episode psychosis in schizophrenia spectrum, who in the inclusion period of the trials are treated for at least 11/2 year by one of the six OPUS teams will be asked to give signed informed consent to participate in the trial.

#### Exclusion criteria

patients whose diagnosis was evaluated retrospectively and found not to fulfil the criteria for first-episode psychosis in the F2-spectrum (ICD 10) at any time during the first 11/2 year of OPUS treatment, and patients who do not give signed informed consent to participate in the trial. Drug and alcohol misuse will not lead to exclusion. Patients who are mentally retarded in moderate to severe degree are not treated in OPUS teams and are therefore not a part of the inclusions and exclusions criteria.

Randomization will take place approximately six months prior to the termination of the original two-year OPUS treatment. This will allow a gentle transfer to other treatment services for the control group, and allow proper time to plan the future course of treatment for the experimental group. Expected duration of participating in the trial is therefore 3 1/2 year from entry interview to follow-up interview.

### Randomisation

Randomisation will be centralised and computerised with concealed randomisation sequence carried out by the Copenhagen Trial Unit (CTU). Block size will be unknown to the investigators and clinicians. Randomisation will be stratified for treatment site (six sites) and severity of global score on the four of the five domains in SANS, anhedonia, avolition, alogia and affective blunting, with distinction between at least one of the global score measured less than 3 compared to 3 or more. Signed informed consent will be obtained prior to patients being randomized. The allocations concealment is ensured by the investigators call to the randomisation unit, CTU, after completing the collection of baseline data and data needed for the randomisation.

### Interventions

The trial is pragmatic, comparing five years versus two years of specialised, assertive intervention programme (OPUS) defined by a set of protocols.

#### OPUS treatment

The integrated OPUS-treatment consists of three core elements: assertive community treatment, psycho educational family treatment, and social skills training. In addition, the patients receive group intervention to facilitate recovery, cognitive behaviour therapy when indicated, and crisis intervention. All patients are designated a primary staff member, who are responsible for maintaining the contact and to coordinate the treatment within the team, but also coordinate across social services and other institutions involved in the treatment. The pharmacological treatments are guided by official Danish guidelines[15]. The team offers psycho-educational family treatment, and will always try to get in contact with at least one family member and motivate the family to participate in a psycho-educational group. Patients will be visited in their homes or other places in their community or at their primary team member's office according to the patient's preferences. OPUS-treatment is tailored to meet the individual patient's needs.

The OPUS staff consists of a multidisciplinary team, including a psychiatrist, psychologists, nurses, social workers, physiotherapist, and vocational therapist. All team members, except the psychiatrist, function as primary team member for the patients. The patient to staff member ratio is 10:1. All members of the OPUS staff are well educated, and have obtained great experience in first episode psychosis, and are continually trained and supervised in the core elements of the OPUS treatment to provide the specialised assertive intervention.

